### Statistical plan

We will use summary descriptive statistics for the study population. Dichotomous outcomes will be compared between the intervention and comparator groups using Pearson's chi square test and by calculating relative risk. Continuous outcomes will be compared using an independent t test for normally distributed data and Mann Whitney U test for non-parametric data. Cost benefit will be expressed in dollar terms. Patient satisfaction outcomes will be largely descriptive.

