### Outcome measures

#### a. Primary

The primary outcome measure is the proportion of patients requiring one or more episodes of unplanned medical attention (in or out of hospital) in the first 48 hours.

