### Sample size estimates

Based on an estimate of 5% of patients having an unplanned episode of care within 48 hours, to detect non-inferiority defined as a risk ratio no greater than 1.5 between the intervention and control groups a sample size of 940 patients in each group will be required (if α = 0.05 and β= 0.2). We estimate 10% of the 100000 annual ambulance transfers will be eligible for the trial so anticipate being able to recruit the requisite sample size in less than one year.

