## Discussion

This trial is a methodologically rigorous and adequately powered evaluation of an alternative to hospital transfer for low acuity patients calling an ambulance service. There are large potential healthcare benefits in terms of reducing ED overcrowding, increasing paramedic availability, reducing ambulance ramping, cost savings and improving patient satisfaction. The study outcomes will provide important information on the safety and quality of assessment and care in the home for conditions which would otherwise result in a presentation to ED.

This is the first time that paramedics will be involved in a trial in which their assessment determines suitability for handover to a service outside of an ED. The clinical processes and pathways established in the trial will therefore provide evaluated practice as a basis for future health policy.

The trial has one major risk - inferior clinical outcomes associated with either misdiagnosis or inadequate therapy in the intervention arm. Although both paramedic and nurse practitioners are highly experienced health professionals and will have immediate access to specialist and generalist medical practitioners, there will be no medical diagnostician in the direct care of the vast majority of intervention arm patients. However we anticipate with careful patient inclusion and exclusion criteria and well trained staff, that we can select a sufficiently low risk study population and show clinical non-inferiority between the groups. We anticipate benefits to lie in cost savings and patient satisfaction.

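### The trial is sized for non-inferiority at a risk ratio of 1.5, but the only test named for the primary outcome is a chi-square test of no difference, with no stated comparison to that margin

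*Protocol article*

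**What the plan says.** All references are to the protocol article.

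- **Outcome measures, a. Primary.** The primary outcome is binary: "The primary outcome measure is the proportion of patients requiring one or more episodes of unplanned medical attention", counted over the first 48 hours.
- **Sample size estimates.** The starting point is "Based on an estimate of 5% of patients having an unplanned episode of care within 48 hours". The aim is "to detect non-inferiority defined as a risk ratio no greater than 1.5 between the intervention and control groups", and "a sample size of 940 patients in each group will be required" ("if α = 0.05 and β= 0.2"). Whether α is one- or two-sided is not stated.
- **Statistical plan.** One sentence covers all binary outcomes and makes no exception for the primary: "Dichotomous outcomes will be compared between the intervention and comparator groups using Pearson's chi square test and by calculating relative risk". The section does not mention non-inferiority, the margin, a confidence interval or a decision rule.
- **Discussion.** The investigators expect to "show clinical non-inferiority between the groups", and they name inferior clinical outcomes in the intervention arm as the trial's one major risk.

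**The concern.** The hypothesis and the named test do not match. A non-inferiority claim at a risk ratio of 1.5 has to reject the null hypothesis that the true ratio is 1.5 or more. Pearson's chi-square has the null hypothesis that the ratio is 1. Failing to reject equality is not evidence that the excess risk is smaller than the margin. Conversely, a significant chi-square can occur in a trial that meets the margin. A relative risk quoted as a point estimate does not settle the matter either, because it carries no statement of uncertainty relative to 1.5.

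The primary comparison is the trial's main protection against the risk that the Discussion singles out. An analysis plan that carried the Statistical plan sentence forward unchanged would leave that protection untied to the margin on which the sample size rests.

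**Working it through.** **Inputs.** Event risk 5%, margin RR 1.5, α 0.05, β 0.2 and 940 per group, all from Sample size estimates. Assumptions: 5% is the risk in both arms under true equality, and the margin is therefore 7.5% against 5%, or 0.05 × (1.5 − 1) = 0.025 as a difference.

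**1. Reproduce the 940.** Risk-difference formula with one-sided α of 0.05:

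n = (1.645 + 0.842)² × 2 × 0.05 × 0.95 / 0.025² = 6.183 × 0.095 / 0.000625 = 939.7, which rounds up to **940**.

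Alternatives that do not give 940:

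| Calculation | n per group |
|---|---|
| Difference scale, one-sided 0.025 | 1194 |
| Log risk ratio, one-sided 0.05: 6.183 × 2 × (0.95/0.05) / (ln 1.5)² | 1430 |
| Log risk ratio, one-sided 0.025 | 1815 |
| Two-sided superiority chi-square, 5% vs 7.5% | 1471 |
| One-sided superiority chi-square, 5% vs 7.5% | 1159 |

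The sample size is therefore a non-inferiority calculation, one-sided at 0.05, on the risk difference. It is not a chi-square calculation.

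**2. Behaviour of each rule at 940 per arm.** These are exact sums over the two binomial distributions. Chi-square: pooled z, no continuity correction, non-significant if |z| < 1.96. Difference limit: d + z × √[p₁(1−p₁)/n + p₀(1−p₀)/n], compared with 0.025. Risk-ratio limit: exp{ln RR + z × √(1/x₁ − 1/n + 1/x₀ − 1/n)}, compared with 1.5. Here z is 1.645 (one-sided 95%) or 1.960 (two-sided 95%).

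| Rule read as success | True 7.5% vs 5% | True 5% vs 5% |
|---|---|---|
| Chi-square non-significant (two-sided 0.05) | 38.8% | 95.0% |
| Difference, one-sided 95% limit < 2.5 points | 5.1% | 80.0% |
| RR, one-sided 95% limit < 1.5 | 5.0% | 64% |
| Difference, two-sided 95% limit | 2.6% | 70% |
| RR, two-sided 95% limit | 2.6% | 52% |

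The first numeric column is the false-success rate at the margin. The second is the chance of success at true equality.

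**3. The same thing in event counts.** Take 47 control events (5% of 940).

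- Chi-square is non-significant for 31 to 67 intervention events. At 67, RR = 67/47 = 1.43 and p = 0.053. The upper limit is 1.93 (one-sided 95%) or 2.05 (two-sided 95%).
- Largest intervention count that meets the margin: **54** on the difference with a one-sided 95% limit (54 gives 2.46 points, 55 gives 2.57), or 51 with a two-sided 95% limit.
- On the RR: **50** with a one-sided 95% limit (upper limit 1.473), or **47** with a two-sided 95% limit (upper limit 1.483).

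For example, 64 against 47 events gives RR 1.36, p = 0.096 and a 95% interval of 0.94 to 1.96. The chi-square is non-significant, and non-inferiority is not shown on either scale.

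**The case against.** Three points can be made for the plan.

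*The relative risk is planned too.* The sentence that names the chi-square also plans a relative risk, the scale on which the margin is defined. Reported with a confidence limit and set against 1.5, it would answer the question. This stands, and it limits the point: the chi-square and a bare point estimate cannot establish non-inferiority, but the relative risk could if the comparison were stated. A reader might infer that the whole planned analysis is incapable of it. The text does not go that far, since it neither states nor excludes an interval.

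*No rule equates non-significance with success.* This also stands. A reader might infer that p > 0.05 will be reported as non-inferiority. The article nowhere says so, and its only stated criterion is the risk ratio of 1.5. The 38.8% is therefore conditional on a reading that the article does not adopt.

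*This is a condensed article.* Interval type, analysis sets and similar detail are commonly left to a full protocol or analysis plan, and their absence is no criticism here. That does not dispose of the mismatch, because the article is not silent: it names a test for the binary outcomes, and that test addresses a different hypothesis from the one used for the sample size.

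**Conclusion.** The mismatch holds. The design, the sample size and the intended conclusion are all non-inferiority, while the one named test for the primary outcome is of no difference, and nothing links the planned relative risk to 1.5. Misreading a non-significant result is a risk, not something that the plan prescribes. Were it to happen, false success at the margin would be 38.8% against about 5%, assuming a 5% control risk, 940 analysed per arm and a two-sided 0.05 chi-square.

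The 940 is not wrong for its implied inputs. It does rest on two choices that the article leaves unsaid: one-sided 0.05 and the risk-difference scale. These matter for the correction, because the stated 80% power holds only on that basis. The 2.5-point difference and the ratio of 1.5 coincide only when the control risk is 5%.

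**What to change.** For the primary outcome, replace the chi-square with a rule of this kind: non-inferiority is declared only if the upper one-sided 95% confidence limit (the level implied by 940) for intervention against control lies below the margin. State the scale in the same sentence.

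- **Risk difference, limit below 2.5 percentage points.** This matches the sample size and keeps 80% power at 940 per arm. The margin, now defined only as a ratio, must then be stated as a difference.
- **Risk ratio, limit below 1.5.** This keeps the margin as written, but power at 940 per arm is about 64% (52% with a two-sided 95% interval). The 80% must be restated, or the sample raised to about 1430 per arm (about 1815 for a two-sided 95% interval).

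Keep the chi-square for the secondary binary outcomes.

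Cost: the rule is one sentence and needs no new data. On the difference scale the only other change is the wording of the margin. On the ratio scale the cost is either the acknowledged loss of power or about 490 more patients per arm (1430 − 940) at the one-sided 0.05 level.

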## Background

Emergency Department (ED) overcrowding is an international phenomenon[1]. Overcrowding is associated with mortality[2], delay to time critical therapy[3,4], patient dissatisfaction[5] and ambulance ramping, where paramedics are unable to deliver patients to ED due to a lack of available beds.

In Australia, there are over 7 million hospital ED episodes of care per year with up to 25% of patients arriving in ED by ambulance[6]. Estimates of the proportion of these ED cases that are primary care patients vary according to the definition and scope of primary care[7], but a reasonable proportion of cases that present to ED by ambulance may be equally suited to care in the community by a primary care service.

There are many reasons why people call an ambulance in addition to a medical emergency. There may be inability to access alternative health care; issues associated with chronic illness and disability; requirements for advice and reassurance; and psychosocial reasons. Many patients access health care through the ambulance service without necessarily believing they need transport to hospital, yet paramedics in some jurisdictions are governed by the duty of care that requires them to render assistance and care for the patient until they handover to another health service. In practice this means that the patient may be transferred to ED even if the patient does not require emergency care.

There is evidence from cluster and before-after studies that paramedics with extended skills can mange low-risk patients in the community without hospital transfer[8,9]. However other studies using paramedics as an assessment and referral service to divert cases away from ED have yielded conflicting results[10]. This trial has been designed to provide an alternative care path for patients that call an ambulance for minor injury and illness. The aim of the trial is to determine whether paramedic referral to a rapid response primary care service in the patient's own residence is clinically effective, safe and an efficient use of resources.

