#### b. Secondary

1. Proportion of patients requiring 2nd ambulance attendance prior to the arrival of the primary care team.

2. Number of ambulance transports of patients to ED following referral to the intervention.

3. Proportion of patients referred to ED in the control arm that did not wait for assessment/treatment

4. Time to first contact with definitive care provider (ED and home hospital team).

5. Number of investigations performed

6. Number of calls to ambulance call centre within 48 hours.

7. Number of episodes of contact with healthcare providers in next 7 days.

8. Number of episodes of ED attendance within the next 7 days.

9. Hospital admissions within the next 7 days.

10. Adverse events within the next 7 days.

11. Deaths within the next 7 days.

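### If 7-day deaths are very rare, the stated chi-square test and relative risk give no informative bound on excess harm; a risk difference with a score-type interval would

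*Protocol article*

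**What the plan says.** The Statistical plan section of the protocol article has a single rule for binary outcomes, a Pearson "chi square test and by calculating relative risk". It makes no exception for sparse data and names no absolute measure of effect.

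The secondary outcomes include "Deaths within the next 7 days" and "Adverse events within the next 7 days". Death is dichotomous for each patient, so the rule applies to it. The article does not say whether adverse events are a proportion or a count per patient. No expected rate is given for either.

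The Background section sets out to learn whether the referral pathway is "clinically effective, safe and an efficient use of resources". The Discussion section anticipates, given careful eligibility criteria and trained staff, "that we can select a sufficiently low risk study population". The formal non-inferiority question belongs to the primary outcome, the "proportion of patients requiring one or more episodes of unplanned medical attention (in or out of hospital) in the first 48 hours". The Sample size estimates section sizes this at 940 per group from an assumed 5% rate and a risk ratio margin of 1.5.

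**The concern.** A relative risk needs events in the control arm to be finite, and more than a handful in both arms to be precise. Patients chosen to be at low risk may have very few deaths in 7 days. The relative risk may then not exist, or may have an interval so wide that it neither supports nor questions safety. Chi-square adds a p value, or nothing at 0 v 0, but never a bound.

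What a reader wants from a small number of deaths is the largest excess risk that the data still allow. The stated pair of methods does not supply it. The report could then rest on a bare statement that no deaths occurred, or on a non-significant p value. The primary outcome does not fill this gap, because it pools all unplanned contacts and ends at 48 hours.

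**Working it through.** **Inputs.** From Sample size estimates: 940 per group, 5% event rate, risk ratio margin 1.5, α = 0.05, β = 0.2. Assumed, because the document gives no death rate: L = 0.5, 1, 2 or 3 expected deaths per arm, the same in both arms (about 0.05% to 0.3% of 940).

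**1. The plan's own figure.** A risk ratio of 1.5 on 5% is 7.5%, a difference of 0.025. On the difference scale with one-sided α = 0.05 and 80% power:

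n = (1.645 + 0.842)² × 2 × 0.05 × 0.95 / 0.025² = 939.7, rounded up to 940.

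So 940 is reproduced, and is used below as the arm size.

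**2. The primary outcome is not sparse.** Expected events per arm: 0.05 × 940 = 47. At 47 v 47 the relative risk is 1.00, with standard error of its log √(1/47 + 1/47 − 2/940) = 0.201. The 95% interval is exp(±1.96 × 0.201) = 0.67 to 1.48. The stated measure works normally here.

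**3. How often an arm has no deaths.** With Poisson counts, one given arm is empty with probability exp(−L), at least one arm with 1 − (1 − exp(−L))², and both with exp(−2L). The relative risk (intervention over control) is not a finite number whenever the control arm is empty, so the second column below also gives the chance of that.

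| Expected deaths per arm | Control arm empty | At least one arm empty | Both arms empty |
|---|---|---|---|
| 0.5 | 61% | 85% | 37% |
| 1 | 37% | 60% | 14% |
| 2 | 14% | 25% | 2% |
| 3 | 5% | 10% | 0.2% |

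**4. What the stated methods return.**

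- 0 v 0: the relative risk is 0/0 and chi-square cannot be computed.
- Control arm only empty: the relative risk is infinite; chi-square can be computed.
- Intervention arm only empty: the relative risk is 0; chi-square can be computed. The usual log-scale interval does not exist.
- 2 v 2: the relative risk is 1.0, standard error √(1/2 + 1/2 − 2/940) = 0.999, 95% interval exp(±1.96 × 0.999) = about 0.14 to 7.1.

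**5. What a risk difference returns.** Newcombe's upper 95% limit is d + √((u₁ − p₁)² + (p₂ − l₂)²), where d = p₁ − p₂, arm 1 is intervention, arm 2 is control, and l and u are Wilson limits.

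- 0 v 0: Wilson upper limit 1.96² / (940 + 1.96²) = 3.84 / 943.84 = 0.41%. The limit for the difference is 0.41 percentage points.
- 1 v 0: Wilson upper limit for 1/940 is 0.60%. The limit is 0.60 percentage points.
- 2 v 2: p = 0.213%, Wilson limits 0.058% and 0.772%. The limit is √(0.560² + 0.154²) = 0.58 percentage points.

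In all three cases the excess excluded is a definite figure well below one percentage point.

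**The case against.** The best defence is that this is a short paragraph in a journal article. It states a default and forbids nothing. A fallback for sparse tables is often left to a full protocol or analysis plan, which is not shown here, and counts by arm allow an exact bound at any time (0/940 has a two-sided 95% upper limit of 0.39%). That stands in part, and it is why the point is minor. But the article does more than stay silent: it names a test and an effect measure and applies them to every dichotomous outcome, and for deaths a better measure is available at no cost.

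A reader might go further than the document supports in four ways.

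- **That the method fails whenever an arm is empty.** It does not. Chi-square is undefined only at 0 v 0, and the relative risk is a defined 0 when only the intervention arm is empty.
- **That the trial cannot quantify safety.** The formal clinical non-inferiority claim rests on the primary outcome, where about 47 events per arm are expected. Deaths and adverse events are secondary outcomes with no margin attached.
- **That zero counts are to be expected, for adverse events too.** No rate is given for either outcome. At a rate of 0.5% the chance of an empty arm is under 2%. Adverse events may be commoner than that, or may be analysed as counts, in which case this rule would not govern them.
- **That chi-square would raise false alarms.** Single tables look that way: 4 v 0 gives p = 0.045 by Pearson and 0.125 by Fisher's exact test. But over all possible tables at 940 per arm, the false-positive rate of Pearson's test stays below 5% for 0.5 to 5 expected events. The p value is not the main weakness.

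**Conclusion.** The point holds in a limited form. Applied as written to 7-day deaths, the stated analysis gives no informative bound on excess harm if deaths are very rare. The size depends on the assumed rate: the chance of at least one empty arm falls from 85% at 0.5 expected deaths per arm to 10% at 3. Even with no empty arm, two deaths in each leave the relative risk anywhere from about 0.14 to 7.1. If deaths were not rare, the problem would largely disappear. The primary outcome and its sample size are untouched, so this is a minor weakness in one secondary safety analysis and not a failure of the trial's safety aim.

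**What to change.** Add one sentence to the Statistical plan section. For deaths, and for any other dichotomous safety outcome with few or zero events, report the counts by arm and the absolute risk difference with a 95% score-type interval (Newcombe or Miettinen-Nurminen, chosen in advance). State its upper limit as the excess risk excluded, and give the relative risk only where both arms have events.

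The cost is that sentence. It needs no new data, patients or procedures, and the primary analysis is unchanged.

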### Intervention

The intervention arm will be a priority response home hospital service run by the Silver Chain Association of Western Australia that will visit the patient in their own residence within four hours of paramedic referral. A nurse practitioner or clinical nurse specialist will provide the initial episode of care with 24 hour medical cover provided by an on-call roster of general practioners and specialists. Assessment, investigation and treatment as required will occur in the community. After the initial episode of care in their residence the patient may be discharged from the care of the service; have ongoing therapy at home over ensuing days e.g. IV antibiotics; or if needed referred to an ED.

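### Time to first definitive contact is a time-to-event outcome with foreseen non-events, but it falls under a t test or Mann-Whitney rule with no place for control patients who leave ED unseen

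*Protocol article*

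**What the plan says.** In the protocol article, the list of secondary outcomes includes, as item 4, "Time to first contact with definitive care provider (ED and home hospital team"). Item 3 is "Proportion of patients referred to ED in the control arm that did not wait for assessment/treatment".

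The Statistical plan has one sentence that reaches item 4: "Continuous outcomes will be compared using an independent t test for normally distributed data and Mann Whitney U test for non-parametric data". It names no time-to-event method and does not say how a patient without a contact time is counted.

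The Intervention section commits the home team to "visit the patient in their own residence within four hours of paramedic referral", so a 4-hour mark is already part of the trial. The term first contact is not defined as arrival, triage or clinician assessment.

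**The concern.** A t test needs a value for every patient it analyses. Mann-Whitney needs at least a rank. A control patient who walks out before being assessed has neither unless a rule supplies one. Run on recorded times, the comparison is between everyone the home team reached and only those ED patients who stayed long enough to be seen.

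That selection happens after randomisation and depends on the quantity being measured: a patient who leaves unseen had a wait longer than the time at which they left. Removing such patients shortens the observed ED wait. At stake is a comparison of timeliness that could favour ED when the two arms are equally fast.

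**Working it through.** **The plan's own figure.** The only number that could be affected is the sample size: "a sample size of 940 patients in each group will be required (if α = 0.05 and β= 0.2"), from "Based on an estimate of 5% of patients having an unplanned episode of care within 48 hours" and "non-inferiority defined as a risk ratio no greater than 1.5 between the intervention and control groups". A risk ratio of 1.5 at 5% is a margin of 0.05 × 0.5 = 0.025. With one-sided α = 0.05 and 80% power:

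n = (1.645 + 0.842)² × 2 × 0.05 × 0.95 / 0.025² = 6.183 × 152 = 939.7, so 940.

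This reproduces the figure. It rests on the primary outcome alone, so nothing below changes it.

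**Inputs for the time outcome.** The article gives none, so all of these are assumptions: log-normal time to assessment, median 120 min, SD of the log 0.8, hence mean 120 × exp(0.8²/2) = 165 min; 2% to 15% of controls leave unseen; contact means assessment; leavers are omitted.

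**Two models of leaving.**

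- *Independent patience.* Each patient has an exponential patience time, independent of the wait, and leaves if it is shorter than the wait. The rate r solves ∫ f(t)(1 − e^(−rt)) dt = d, where f is the density of the wait and d the proportion leaving. Times among those seen have density f(t)e^(−rt)/(1 − d).
- *Longest waiters leave.* The median among those seen is the (1 − d)/2 quantile of the full distribution, 120 × exp(0.8 × z), with z the normal quantile at (1 − d)/2. At d = 0.10, z = −0.126 and the median is 108.5.

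Simulated values, in minutes, with the calculated median in brackets:

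| Leaving | Independent patience: median seen | Mean seen | Longest leave: median seen | Mean seen |
|---|---|---|---|---|
| 0% | 120 | 165 | 120 | 165 |
| 2% | 118 (118.6) | 162 | 117 (117.6) | 150 |
| 5% | 116 (116.5) | 158 | 114 (114.1) | 139 |
| 10% | 113 (113.1) | 151 | 108 (108.5) | 125 |
| 15% | 110 (109.7) | 145 | 103 (103.2) | 115 |

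If patients are lost for reasons unrelated to the wait, the median stays at 120.

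A second assumed set (median wait 90 min, log-SD 0.8, log-normal patience with median 360 or 240 min) gives 11.0% or 19.2% leaving and a median among those seen of 81.4 or 75.9 min. At about 10% leaving, the shift is therefore 8.6/90 = 10% here against 7/120 = 6% above. The size depends on the inputs; the direction does not.

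**Effect on the tests.** With 940 per arm, identical waiting times in both arms and 500 simulated trials per setting, a two-sided 5% test should favour ED in 2.5% of trials. On seen patients only it did so in:

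| Leaving | Independent: Mann-Whitney | Independent: t test | Longest leave: Mann-Whitney | Longest leave: t test |
|---|---|---|---|---|
| 2% | 5% | 6% | 12% | 59% |
| 5% | 9% | 15% | 43% | 98% |
| 10% | 35% | 50% | 93% | 100% |
| 15% | 68% | 85% | 100% | 100% |

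**Candidate repairs under independent patience.** A Mann-Whitney with leavers ranked last favoured home care in 10%, 18%, 63% and 95% of trials at 2%, 5%, 10% and 15% leaving, because it scores leaving as the worst wait.

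Cumulative incidence divides the number seen by time t by everyone randomised, (1 − d) times the distribution among those seen. Half of all randomised controls are then seen by 121, 123, 126 and 130 min, the time t solving ∫₀ᵗ f(u)e^(−ru) du = 0.5. At 10% leaving, 75% of all randomised are seen by 4 hours, against 83% of those seen and Φ(ln 2/0.8) = 81% had nobody left. This measure also counts leaving against ED, but it does so openly, as a proportion not seen.

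**The case against.** The strongest reply is that the article never says leavers are excluded. One generic sentence on tests is what a condensed article carries, and handling of missing values can sit in a full protocol or SAP that is not shown. A reader might infer that the plan drops these patients; the text does not support that, and omission is only what follows if the named tests are run on recorded times. Nor can it be said that neither test could keep them, since Mann-Whitney can if leavers are ranked last. What remains is a choice the article does state: a family of tests for fully observed values, covering an outcome with non-events that the same list foresees.

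Second, if contact means ED arrival or triage, leavers have a time and the bias vanishes. That stands. The words definitive care provider point towards assessment but do not settle it.

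Third, a reader might take secondary outcome 1, "Proportion of patients requiring 2nd ambulance attendance prior to the arrival of the primary care team", as proof of the same gap in the intervention arm. It is not. A second attendance is not a transport, a patient not transported can still be seen by the home team, and a patient taken to ED meets a provider that outcome 4 names.

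Fourth, it is tempting to call timeliness central to the case for the new pathway, or to say that leavers are the longest waiters. The Discussion expects the benefits in cost and patient satisfaction, and nothing in the article describes who leaves. Neither claim is needed. The bias would also run against home care, so it could not create a spurious advantage for it.

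**Conclusion.** The concern holds in a limited form. The stated tests do not suit secondary outcome 4 as the protocol sets it up. On two conditions that the article leaves open (contact means clinician assessment, and the tests use recorded times only), ED waits are biased short. The direction follows from leaving before being seen and appears under both leaving models.

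The size cannot be known from the article. Under the assumed 120-min median with independent patience, the shift in the median is about 2 min at 2% leaving, 7 min at 10% and 10 min at 15%. It is minor at the low end; with 940 per arm it is enough to mislead the tests at around 5% to 10%. One secondary outcome is affected. The primary outcome and its sample size are not.

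**What to change.** - Define first contact as assessment by a treating clinician, in ED or from the home hospital team, timed from randomisation in both arms.
- For this outcome, replace the t test or Mann-Whitney with the cumulative incidence of being seen among all randomised patients. Treat leaving unseen as a competing event, so leavers count as not seen, and apply the same rule to intervention patients never reached by a provider.
- Report for each arm the median time (when half of all randomised patients have been seen) and the proportion seen by 4 hours. The latter can use the relative risk already planned for dichotomous outcomes.
- Keep a worst-rank Mann-Whitney, if wanted, as a sensitivity analysis only, labelled as a composite because it can lean towards home care.

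The cost is wording. Contact times and the did-not-wait status are already outcomes, and departure times are not needed when leavers are counted as never seen. This assumes that the call centre records the time of randomisation; a flag for intervention patients never reached should be added if there is none. The small downside is that the outcome then measures being seen at all as well as speed, and it must be described that way.
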